### Randomization and blinding

Randomization will take place at the cluster (i.e., ward) level, in order to minimize contamination effects inherent to the nature of the intervention in case the randomization was performed at the patient or physician level [55]. The investigators will determine seven pairs of comparable wards (regarding the treatment spectrum, the size of the ward, etc.) and then randomize one ward of each pair either to the intervention or to the control group. While the principal investigators will determine the paired wards, the randomization will be conducted by a blinded investigator independent to the study using the coin toss method. However, due to the nature of the intervention (use of the SDM-assistant vs. TAU), there will be no blinding between intervention and control wards.

### Data analysis

The effect-size for continuous outcomes will be the mean difference (MD) and for dichotomous outcomes will be the odds ratio (OR), presented with their 95% confidence intervals. Per-protocol analysis will be conducted, i.e., by excluding patients with no outcome data, patients that do not receive at least one session of SDM-assistant, patients who moved from a ward belonging to the control group to a ward belonging to the intervention group or vice versa. There will be no imputation of missing outcome data, and observed cases will be used.

The primary outcome (SDM-Q-9 at T1) and secondary continuous outcomes will be analysed with mixed-effects linear regression models fitted with ward (cluster) as a random-effects term and with intervention/control group as a fixed-effects term. In a similar vein, dichotomous outcomes will be analysed with logistic regression models using the generalised estimating equations (GEEs).

The robustness of the results of the primary outcome will be investigated in a sensitivity analysis by adjusting for baseline covariates such as severity of illness, admission status and variables with a large baseline imbalance.

In addition, we plan exploratory subgroup analyses in order to investigate if there is potential effect-modification of patient characteristics (e.g., age, sex, symptom severity, duration of illness) on the primary outcome.

Alpha will be set at two-sided alpha of 0.05.

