**Methods:**

The planned matched-pair cluster-randomised trial will be conducted in acute psychiatric wards (*n* = 14 wards planned) and will include adult inpatients with schizophrenia or schizophrenia-like disorders (*N* = 252 participants planned). On the intervention wards, patients and their treating physicians will use the SDM-assistant, whenever a decision on choosing an antipsychotic is warranted. On the control wards, antipsychotics will be chosen according to treatment-as-usual. The primary outcome will be patients’ perceived involvement in the decision-making during the inpatient stay as measured with the SDM-Q-9. We will also assess therapeutic alliance, symptom severity, side-effects, treatment satisfaction, adherence, quality of life, functioning and rehospitalizations as secondary outcomes. Outcomes could be analysed at discharge and at follow-up after three months from discharge. The analysis will be conducted per-protocol using mixed-effects linear regression models for continuous outcomes and logistic regression models using generalised estimating equations for dichotomous outcomes. Barriers and facilitators in the implementation of the intervention will also be examined using a qualitative content analysis.

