### Intervention and control group

Antipsychotic drugs are recommended for the treatment of acute episodes of schizophrenia [4]. Therefore, decisions on choosing which antipsychotic drug to be used are necessary in acute psychiatric wards. In the intervention group, whenever a decision on choosing an antipsychotic is warranted (e.g., initiation, continuation or change of antipsychotic drugs), patients and their treating physicians will use the SDM-assistant in the context of a shared-decision-making process for the selection of an antipsychotic, in addition to the usual care. The SDM-assistant can be used more than once in different sessions during the trial. In the control group, patients and their treating physicians will not use the SDM-assistant, and antipsychotics will be chosen according to treatment-as-usual (TAU). Changes in the treating physicians will be discouraged, yet, when necessary, they will be recorded. In addition, we will use cluster randomization at the ward level, and therefore, a possible switch to a physician from the other arm of the trial would be unlikely. We will consider as protocol violations when patients do not receive at least one session of the SDM-assistant or when patients switch from the control to the intervention group or vice versa.

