### Outcomes

Recruitment and data collection will take place at the participating wards. Baseline data will be measured at inclusion and before using the SDM-assistant (T0). Then, the aim is that patients and physicians will use the SDM-assistant at least once during inpatient stay whenever a decision on choosing an antipsychotic is warranted, but no later than three weeks after admission. Both will also be encouraged to use the SDM-assistant as often as possible. At the time of discharge from the hospital, outcomes will be measured (T1). Three months after the discharge, we will contact each patient and the treating outpatient psychiatrist via telephone and/or post in order to obtain follow-up outcome data (T2). Table 1 presents a schematic diagram of participant timeline and data collection. Scales (German versions) could be filled accordingly by patients, their treating physicians or the study personnel (e.g., clinical psychologists not involved in the treatment of the patients and trained to administer the scales). Physicians and study personnel will receive training on the use of individual scales.

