Third, there are certain difficulties in the implementation of the intervention. Shared-decision making can be successful, yet challenging, in acutely ill inpatients with schizophrenia, potentially due to reduced decisional capacity, high severity psychotic symptoms, cognitive impairment, lack of insight, and negative attitudes towards the treatment [64–66]. The use of the SDM-assistant could make the process even more demanding due to the higher attention and cooperation requirements. For these reasons, we will use a mixed-methods approach to evaluate barriers and facilitators for the implementation of the intervention. SDM-assistant aims to enable patients to get familiar with the evidence and participate in the decision-making, without forcing them to be involved. In those cases, a more paternalistic decision-making approach with the physician choosing a suitable medication might be still acceptable [18]. Nevertheless, the early involvement of patients in the selection of antipsychotics can be very important in order to prevent burdensome side-effects, since at least some of them could be subjectively realized only later after the improvement of symptoms, e.g. rapid weight gain [67]. Third, treatment-as-usual will be used in the control group, instead of an active control group (e.g., using paper forms to present evidence on antipsychotics or unspecific group training) in order to avoid contamination. However, it is possible that the increased attention in the intervention group could inflate any differences found.

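### The only stated analysis is per-protocol, with a no-session exclusion that can act on intervention wards alone, so the primary comparison is not between the groups as randomised and probably favours the SDM-assistant

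*Protocol article*

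**What the plan says.** The abstract fixes the approach: "The analysis will be conducted per-protocol using mixed-effects linear regression models for continuous outcomes". The Data analysis section defines it as "excluding patients with no outcome data, patients that do not receive at least one session of SDM-assistant", plus patients who moved between a control and an intervention ward. It adds: "There will be no imputation of missing outcome data, and observed cases will be used".

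The section Intervention and control group treats the same event as a breach: "We will consider as protocol violations when patients do not receive at least one session of the SDM-assistant". It also says: "In the control group, patients and their treating physicians will not use the SDM-assistant".

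The Outcomes section gives the aim for intervention patients, which is use of the tool "at least once during inpatient stay whenever a decision on choosing an antipsychotic is warranted, but no later than three weeks after admission". The session therefore comes after ward randomisation and after baseline.

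The one sensitivity analysis described for the primary outcome adjusts for baseline covariates, including illness severity and admission status. It does not change who is analysed. An analysis of all patients by the arm of their ward is not mentioned anywhere.

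**The concern.** Having a session is something that happens, or fails to happen, after allocation, and it can be observed in one arm only. Dropping intervention patients without a session leaves their counterparts on control wards in the analysis, because nobody can identify them. The two analysed groups then differ in composition even if the wards were perfectly matched.

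The primary outcome is the patient's own rating of involvement (SDM-Q-9 at discharge). The Discussion says that shared decision-making can be hard in this population, "potentially due to reduced decisional capacity, high severity psychotic symptoms, cognitive impairment, lack of insight" and negative attitudes to treatment, and that the tool may add to the demands. If patients with these features more often have no session and also feel less involved, removing them raises the intervention mean without any effect of the tool. The trial's question is the SDM-assistant against usual care on acute wards, and failure to complete a session is part of the answer.

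This is a stated choice of primary population. It is not a detail left for a statistical analysis plan.

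**Working it through.** **Inputs from the protocol (Sample size and recruitment).** 180 patients analysed in 12 clusters, so 90 per arm and 15 per cluster; ICC 0.02; d = 0.45-0.5; two-sided alpha 0.05; power at least 80%; 252 recruited from 14 wards.

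**The plan's own figure.**
- Design effect = 1 + (15 - 1) x 0.02 = 1.28.
- Effective n per arm = 90/1.28 = 70.3.
- Non-centrality = d x sqrt(70.3/2) = d x 5.93.
- Power at 180 (normal approximation): 76.1% at d = 0.45, 80.4% at d = 0.475, 84.2% at d = 0.5.

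The stated 180 is thus reproduced at the middle of the stated range. The shortfall at d = 0.45 is a separate matter.

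**Bias from the exclusion when the tool has no effect.** Let p be the share of intervention patients without a session, and s the amount by which their SDM-Q-9 is lower, in SD, than that of patients with a session. The full-arm mean is lower than the session-only mean by p x s. Control wards keep the full mix, so the spurious difference is p x s. The protocol gives neither p nor s; the values below are assumptions.

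| p | s | Spurious difference (SD) | Non-centrality (x 5.93) | Type I error, normal, 90 v 90 |
|---|---|---|---|---|
| 10% | 0.3 | 0.03 | 0.18 | 5.4% |
| 20% | 0.5 | 0.10 | 0.59 | 9.1% |
| 30% | 0.8 | 0.24 | 1.42 | 29.6% |

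Type I error = Phi(nc - 1.96) + Phi(-nc - 1.96), where nc is the non-centrality. The middle row's 0.10 SD is 20-22% of the planned effect (0.10/0.5 to 0.10/0.45).

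**Stricter version.** Reduce the intervention arm to 90 x (1 - p), with 15 x (1 - p) per ward in the design effect, and use a t reference with 10 degrees of freedom for 12 clusters. The three type I errors become about 5.3%, 8% and 22%.

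**A different selection model.** Remove the lowest fraction q of the intervention arm on a latent trait that correlates r with SDM-Q-9. Then q = 10%, r = 0.3 gives d = 0.06 (type I error about 6.4%); q = 25%, r = 0.3 gives 0.13 (about 11%); q = 25%, r = 0.5 gives 0.21 (about 23%). With r = 0 there is no bias.

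**Power if everyone is analysed by allocated ward.** If the share q without a session gains nothing, the effect becomes d x (1 - q).

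| q | Diluted d | Power, 180 analysed | Power, all 252 analysed |
|---|---|---|---|
| 10% | 0.405-0.45 | 67-76% | 79-87% |
| 25% | 0.34-0.375 | 52-60% | 64-73% |

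For 252 in 14 wards there are 18 per ward and the design effect is 1 + 17 x 0.02 = 1.34. All power figures use the normal approximation.

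**The case against.** The strongest reply is that the direction of bias is not shown. A reader might infer that the protocol itself identifies patients without a session as the sicker ones, so that the result is certainly biased towards the tool. It does not say that. The Discussion describes why shared decision-making can be difficult, not who will go without a session. Because sessions are tied to a pending choice of antipsychotic, patients with no such decision or an early discharge could also be removed, and they may be less ill. Eligibility also requires the ability to consent, which keeps the least capable out of both arms. This stands: the direction is a reasonable inference, not a fact.

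The planned adjustment for severity and admission status addresses one likely driver of selection and may reduce the bias. It does not bring the excluded patients back or cover capacity, insight and attitudes unless these happen to be added as covariates.

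Three other strong readings are not supported:
- The three-week limit might be taken as part of the exclusion. It is an aim in the Outcomes section; the exclusion concerns patients with no session at all.
- The same bias might be assumed for every secondary outcome. Only the exclusion is shared; side-effects, length of stay or readmission may relate differently to having no session.
- Taken word for word, the rule would empty the control arm. The description of the control group makes it clear that this is not intended.

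The exclusions for missing outcomes and for changing arm apply to both arms and are not this one-sided problem.

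Finally, the assumed inputs have no source in the protocol, and at the low end the inflation is negligible. That limits the claim about size but not the claim about the design of the comparison.

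**Conclusion.** The point holds. As soon as one intervention patient has no session, the analysed groups are not the randomised groups, and no stated analysis restores them. That part follows from the text alone. Bias in favour of the SDM-assistant is likely but not certain. Its size is unknown: 0.03-0.24 SD, with type I error from about 5% to 20-30%, under the assumption that 10-30% have no session and would score 0.3-0.8 SD lower, at the planned 180 patients and ICC 0.02. The secondary outcomes are subject to the same exclusion, with size and direction not established. Because it affects the primary comparison, this should be corrected before analysis.

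**What to change.** - Make the primary analysis by allocated ward: all enrolled patients with discharge data, in the arm of the ward on which they were enrolled, whether or not they had a session or moved.
- Attempt the discharge assessment in every enrolled patient, including those without a session.
- Keep the per-protocol analysis as supportive only, and report how many patients it drops in each arm and why.
- Amend the abstract and the Data analysis section to match.
- Re-check and restate the power, allowing for patients without a session.

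An estimate of the effect in users (complier-average, with ward allocation as instrument) is optional. It needs a caveat: physicians on intervention wards are trained in shared decision-making and evidence-based medicine, so allocation may affect patients who never have a session.

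The change needs no new data collection, since the discharge assessment is already scheduled. The real cost is a diluted effect and the lower power shown above, which may call for a larger sample or a candid statement of the power available.

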**Fig. 1 Fig1:**
[figure not shown]
Potential outcomes of SDM-assistant for choosing antipsychotics

The planned cluster-randomized-controlled trial aims to compare the effects of SDM-assistant versus treatment-as-usual (TAU) in inpatients with schizophrenia. We will investigate whether the SDM-assistant can improve perceived shared-decision-making, lead to fewer side-effects and better adherence at discharge and three-months after discharge. We will also explore factors that could have an impact on the use and effects of the SDM-assistant tool.

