Side-effects will be recorded using items of the clinician version of the Udvalg for kliniske undersøgelser scale (UKU-SERS) [47] at T0, T1 and T2. The UKU scale consists of 48 items covering a comprehensive list of side-effects grouped in four categories, i.e., psychic, neurologic, autonomic and other side-effects. We will also evaluate two additional items about suicidality and oedema. Each item is scored from 0 to 3 based on the severity with a higher score indicating more severity [47]. It will be administered via a semi-structured interview by the study personnel. The weight of patients will be measured at T0 and T1, and we will ask the patients to report their weight at T2. Furthermore, we developed the patient-reported antipsychotic and antidepressant side-effect scale (ANTISIDES) that will be administered at T0, T1 and T2. The scale consists of 41 items covering a broad spectrum of side effects that can be caused by psychotropic drugs. Each item will be rated on a visual analogue scale from 0 “not at all” to 10 “extremely strong”, supplemented by an assessment of the impairment experienced due to the respective side effect (eAppendix 3).

We will address global functioning using the clinician-rated Social and Occupational Functioning Assessment Scale (SOFAS) [48] at T0, T1 and T2, and quality of life using the patient-reported EUROHIS-QOL [49] at T2.

Treatment satisfaction, attitudes and adherence will be measured using the patient-reported scales Questionnaire on Patients’ Treatment Satisfaction (ZUF8) [39], Medication Satisfaction Questionnaire (MSQ) [50], Drug Attitude Inventory (DAI) [51] and Medication Adherence Rating Scale (MARS) [52] at T0, T1 and T2. Physicians will also rate adherence to the medication treatment at T1 and T2 using a single question scored on a 4-point Likert scale from 1 “very good” to 4 “poor”.

Last, data about the use of the SDM-assistant (e.g., number of sessions, duration of use) will be recorded within the SDM-assistant and evaluated at T1. This information would also be helpful in assessing treatment integrity.

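### The stated model has no patient or visit term, so the natural reading is that three-month (T2) estimates of secondary outcomes discard the discharge (T1) data of patients lost afterwards

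*Protocol article*

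**What the plan says.** In the protocol article, Data analysis, a single model is given for every continuous outcome, primary and secondary alike: "mixed-effects linear regression models fitted with ward (cluster) as a random-effects term and with intervention/control group as a fixed-effects term". No patient effect, visit, group-by-visit term or baseline value is named. Baseline adjustment appears only as a sensitivity analysis of the primary outcome. The same section states "There will be no imputation of missing outcome data, and observed cases will be used" and "Per-protocol analysis will be conducted, i.e., by excluding patients with no outcome data".

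Under Secondary outcomes and other variables, most secondary measures are taken at both post-baseline times, for example "Medication Adherence Rating Scale (MARS) [52] at T0, T1 and T2". The Background ends with the aim of finding out whether the tool can "lead to fewer side-effects and better adherence at discharge and three-months after discharge". The abstract says "Outcomes could be analysed at discharge and at follow-up after three months from discharge". No section says that each visit is analysed alone, and none describes a joint analysis of T1 and T2.

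**The concern.** A model with only ward and group suits one visit at a time. Combined with observed cases, this means that the T2 comparison rests only on patients reached after discharge and uses nothing that the others showed at T1.

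That comparison is unbiased only if loss after discharge is unrelated to the patient's state, or related to it in a way that cancels between arms. A joint likelihood-based model needs the weaker condition that loss depends only on observed data, including T1.

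Loss at T2 is foreseeable. Patients leave an acute ward and are then contacted by telephone or post (Outcomes section). Wards are not blinded, and the intervention is meant to change satisfaction and adherence, so loss could plausibly differ by arm. At stake are the three-month secondary results, which the article names as part of its aim.

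**Working it through.** **1. Which outcomes are affected.** From Secondary outcomes and other variables:

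| Post-baseline visits | Measures | Count |
|---|---|---|
| T1 and T2 | UKU-SERS, ANTISIDES, weight, SOFAS, ZUF8, MSQ, DAI, MARS, physician-rated adherence | 9 |
| One visit only | SDM-Q-Doc, PANSS-6, length of stay (T1); EUROHIS-QOL, readmission (T2) | 5 |

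So 9 of the 14 measures with a stated visit are taken twice after baseline. The text gives no visit for the three CGI scales, and Table 1 is not shown; if none of the three is taken at both visits, the count is 9 of 17. The first eight also have a T0 value. Physician-rated adherence has four categories and no T0 value.

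**2. The plan's own figure.** The plan gives no figure for T2. Its sample size is for SDM-Q-9 at T1: 180 patients in 12 wards, or 15 per ward, with ICC 0.02. The design effect is 1 + (15 − 1) × 0.02 = 1.28. At d = 0.475, the middle of the stated range, 70 per arm before clustering gives 2 × 70 × 1.28 = 179.2, which reproduces 180. Nothing below changes it.

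**3. Precision at T2.** Let n patients be seen at T1, a fraction f of them be lost before T2, and ρ be the T1–T2 correlation within patients. Both f and ρ are assumed. The only drop-out figure, 15–25% in Sample size and recruitment, is not split by visit; it is borrowed here for f.

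- Observed cases: variance of a T2 mean = s² / [n(1 − f)].
- Using T1: variance = s² × [(1 − ρ²) / (n(1 − f)) + ρ² / n].
- Ratio = (1 − ρ²) + ρ²(1 − f) = 1 − fρ².

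| f | ρ = 0.3 | ρ = 0.5 | ρ = 0.7 |
|---|---|---|---|
| 0.15 | 0.987 | 0.963 | 0.927 |
| 0.25 | 0.978 | 0.938 | 0.878 |

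The saving is about 1 to 12% of variance. Since √0.9865 = 0.993 and √0.8775 = 0.937, intervals narrow by about 1 to 6%.

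This is patient-level variance; ward variance is not reduced. With 7 wards per arm, ICC 0.02 and all 126 per arm seen at T1, the case f = 0.25, ρ = 0.7 gives:

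- patient part 2 × 0.98 / 94.5 = 0.0207
- ward part 2 × 0.02 / 7 = 0.0057
- ratio (0.0207 × 0.8775 + 0.0057) / (0.0207 + 0.0057) = 0.90

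The top of the range is then nearer 10%.

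**4. Bias at T2.** Simulation with assumed inputs: 252 patients in 14 wards, all seen at T1; ICC 0.02; true difference 0.30 SD at both visits; about 24% missing T2, with loss more likely at lower T1 scores; 1,500 runs per setting. The analysis using T1 regresses T2 on T1 within each arm among those observed, then evaluates the line at the T1 mean of all patients in that arm. It stands in for the full mixed model.

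| Loss depends on T1 | ρ | Observed cases | Using T1 |
|---|---|---|---|
| Same way in both arms | 0.3 | 0.297 | 0.304 |
| | 0.5 | 0.292 | 0.303 |
| | 0.7 | 0.280 | 0.298 |
| In control arm only | 0.3 | 0.248 | 0.298 |
| | 0.5 | 0.226 | 0.309 |
| | 0.7 | 0.192 | 0.305 |

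The standard deviation of the estimates was 0.158 to 0.166 for observed cases and 0.155 to 0.165 using T1, so the precision gain was small here too. With one-sided loss the bias is 0.05 to 0.11 SD, roughly a third to two thirds of one standard error. With the same mechanism in both arms it is at most 0.02 SD.

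**The case against.** The strongest reply is that the article does not say that each visit is analysed alone. It is a condensed report, and visit terms and covariance structures are commonly left to an analysis plan that is not shown. The rule on observed cases does not exclude a joint model either, since a likelihood-based one also uses only observed values and imputes nothing. Separate analyses per visit are common and answer the aim as worded. The gain is modest and its inputs are assumed. Some T2 information also comes from the outpatient psychiatrist.

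Much of this stands. Separate analysis is an inference, and the sponsor may only need to confirm or amend the wording. But the point rests on terms and a missing-data rule that the article does state, and under those a patient lost after T1 drops out of the T2 contrast. The outpatient psychiatrist cannot supply the patient-reported scales.

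Two stronger readings are tempting and are not supported:

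- A reader might infer that T1 and T2 rows would be pooled as if independent, with badly inflated error. Nothing says that visits are pooled, and the ward random effect would absorb most of the resulting correlation between rows.
- A reader might fault the plan for not testing whether a discharge effect persists. No such hypothesis is stated; the aim is a group effect at each of two times.

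**Conclusion.** The point holds as a low-priority improvement for secondary outcomes only. On the natural reading of the stated model, T2 estimates discard T1 data already collected on patients lost after discharge, although the three-month effect is a stated aim.

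The precision gain from using those data is about 1 to 12% of T2 variance, for assumed loss of 15 to 25% and correlation of 0.3 to 0.7. The more useful gain is protection against bias, but material bias requires that loss depends on the T1 state differently in the two arms; otherwise there is little. Neither the correlation nor the T1-to-T2 loss is in the documents. SDM-Q-9 at T1 and the sample size are unaffected.

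**What to change.** For each continuous outcome taken at both T1 and T2, fit one likelihood-based mixed model to both visits:

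- fixed effects for group, visit and group-by-visit, plus the T0 value where it is collected;
- a random ward effect;
- a within-patient covariance, either unstructured for the two visits or a patient random intercept. For weight, measured at T1 but self-reported at T2, the unstructured form allows the variances to differ.

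Report the group difference at T1 and at T2 from this model. Say that, for these outcomes, patients without outcome data means those with neither T1 nor T2, so that a patient seen only at T1 stays in. Keep the T1 model for SDM-Q-9. If separate analyses are preferred, say so and justify observed cases at T2.

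The cost is a few lines of wording and slightly more modelling; no new data and no imputation are needed. The analysis then relies on loss being at random given the observed data, the covariance must stay simple with 14 wards, and outcomes taken only at T2 (EUROHIS-QOL, readmission) are not helped.

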### Sample size and recruitment

The target sample size is *N* = 252 patients from *n* = 14 clusters (126 participants from 7 intervention wards and 126 participants from 7 control wards). Power calculation estimated *N* = 180 participants (*n* = 12 clusters) to be analysed in order to detect an expected Cohen’s d of 0.45–0.5 in the primary outcome of SDM-Q-9 with a power of at least 80% at two-sided alpha of 0.05 assuming ICC = 0.02. These assumptions are based on data from a comparable study (SDM-PLUS), which involved a similar population and the same main outcome parameter [38]. Due to an assumed drop-out rate of patients of 15–25% and to account for a potential drop out of clusters, we aim at recruiting *n* = 14 clusters and *N* = 252 patients.

Patient recruitment will be conducted by a trained study staff and will take place on the 14 selected wards at three hospitals in Munich, Germany (Klinikum rechts der Isar of the Technical University of Munich, kbo-Isar-Amper-Klinikum München-Ost and München-Schwabing). These hospitals with more than 1500 beds in total can facilitate the enrolment of the planned number of patients (*N* = 252) in a timely manner, as in our previous trials [38, 54].

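### Wards are randomised within seven matched pairs, but the primary model has no pair term, so its standard error is too large to the extent that pairing explains between-ward variance

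*Protocol article*

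**What the plan says.** The abstract names the design: "The planned matched-pair cluster-randomised trial will be conducted in acute psychiatric wards". The section Randomization and blinding says that the investigators will form "seven pairs of comparable wards (regarding the treatment spectrum, the size of the ward, etc.) and then randomize one ward of each pair" to intervention or control, by coin toss. The allocation therefore has a built-in restriction: each pair contributes exactly one ward to each arm.

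The Data analysis section gives the terms of the model for the primary outcome (SDM-Q-9 at discharge) and the continuous secondary outcomes: "fitted with ward (cluster) as a random-effects term and with intervention/control group as a fixed-effects term". Dichotomous outcomes get logistic regression with generalised estimating equations, and pair is not mentioned there either. The one planned sensitivity analysis of the primary outcome works by "adjusting for baseline covariates such as severity of illness, admission status and variables with a large baseline imbalance". Neither pair nor the matching factors are named. The section Sample size and recruitment does not mention pairing, and no reason is given for leaving it out of the analysis.

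**The concern.** A model with ward and arm alone treats the 14 wards as if seven had been drawn freely for each arm. Under the randomisation described, whatever the two wards of a pair have in common (treatment spectrum, size and so on) is present once in each arm and drops out of the treatment contrast. The model cannot see this. It puts the shared part into the between-ward variance and so into the standard error.

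At stake is whether the confidence interval and p-value match the allocation that was carried out. If the matching is informative, intervals are wider than the design warrants. There is also a question of timing: a choice between models with and without pair, if made once outcomes are known, would be open to the charge of being data-driven.

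This is not a detail left to a separate analysis plan. The article states the model's terms, and they do not fit the randomisation stated in the section before.

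**Working it through.** **1. The plan's own figure.** Inputs from Sample size and recruitment: 180 patients in 12 wards (15 per ward), d = 0.45 to 0.5, 80% power, two-sided alpha 0.05, ICC 0.02. Design effect: 1 + (15 − 1) × 0.02 = 1.28. At the midpoint, d = 0.475:

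- n per arm = 2 × (1.96 + 0.84)² / 0.475², which rounds up to 70.
- 2 × 70 × 1.28 = 179.2, that is 180 in whole wards of 15.

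The stated 180 is reproduced with no allowance for pairing. The ends of the range give 200 (d = 0.45) and 162 (d = 0.5).

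**2. Setting for the check.** Seven pairs, m = 15 analysed patients per ward. This is the planned 180/12, and close to 18 recruited per ward (252/14) less 15% drop-out (18 × 0.85 = 15.3). Outcome SD = 1. Let r be the share of between-ward variance that pairing explains. The documents do not give r, so 0.25 to 1 is an assumed range.

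**3. Formulas.**

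- Variance that the ward-only model reports on average: 2[ICC + (1 − ICC)/m]/7.
- True variance under within-pair randomisation: 2[ICC(1 − r) + (1 − ICC)/m]/7.

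**4. Numbers at ICC 0.02, m = 15.** (1 − ICC)/m = 0.98/15 = 0.0653.

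- Ward-only SE: √(2 × 0.0853/7) = 0.156.
- At r = 0.5, true SE: √(2 × 0.0753/7) = 0.147. Ratio √(0.0853/0.0753) = 1.06.

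| r | True SE | Ward-only SE too large by | Type I error, 12-df t-test on ward means (simulation) |
|---|---|---|---|
| 0.25 | 0.152 | 3% | 4.6% |
| 0.5 | 0.147 | 6% | 4.0% |
| 0.75 | 0.142 | 10% | 3.5% |
| 1 | 0.137 | 14% | 3.1% |

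The last column comes from 60,000 simulated trials. Averaging the same test's rejection probability over the distribution of its pooled variance gives 4.4%, 3.9%, 3.4% and 2.9%. The small differences do not matter: the level falls to roughly 4.5% to 3%.

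With m = 18 (no drop-out) the excess in SE is 4% to 17%. If the true ICC were 0.05 (an assumption; the protocol gives only 0.02), it is 6% to 34% at m = 15.

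**5. Power.** A ward-mean analysis with pair as a fixed effect has 6 degrees of freedom, against 12 without pair. At d = 0.45, m = 15:

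| ICC | r | Paired, 6 df | Unpaired, 12 df |
|---|---|---|---|
| 0.02 | 0.5 | 72.5% | 76.5% |
| 0.02 | 1 | 78.3% | 77.7% |
| 0.05 (assumed) | 0.5 | 65.8% | 64.8% |
| 0.05 (assumed) | 1 | 79.5% | 66.9% |

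At the plan's ICC the strict paired test loses power at r = 0.5 and is barely ahead with perfect matching. At a higher ICC the balance moves towards pairing.

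**The case against.** The strongest reply is that breaking the match can be a reasonable choice with only seven pairs. The ward-only model keeps about twice the between-ward degrees of freedom. It also copes easily with the loss of a ward, which the sample size section anticipates. Its error is on the safe side. Nothing in the protocol shows that ward size and treatment spectrum explain much of the ward variance in SDM-Q-9; at r = 0.25 the excess in SE is only 3%.

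Most of this stands, and it limits the point. A reader might infer three stronger things that the documents do not support.

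- That the benefit of matching is lost. It is not: matching still balances the arms and reduces the true variability of the estimate. Only the reported precision misses the gain.
- That the analysis is invalid. Omitting pair neither biases the estimate nor raises the false-positive rate.
- That power is certainly thrown away. Wald-test simulations suggest a gain of about three points at ICC 0.02 and d = 0.5, but Wald tests are not a sound basis here. With small-sample degrees of freedom (14 patients per ward, r = 0.5, d = 0.5) the sign depends on the rule. With 12 against 6 df, power is 81.6% without pair and 78.4% with it. If the df rise when a variance component is estimated as zero, the figures are 82.6% and 85.4%.

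The reply does not remove the mismatch. The protocol adopts matching as a design feature, specifies a model that ignores it, and gives no reason.

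**Conclusion.** The point holds as a mismatch between design and analysis, and it is conservative in direction. At the protocol's ICC of 0.02 it is modest: an SE about 3% to 14% too large and a type I error of roughly 4.5% to 3% instead of 5%. These figures rest on assumed pair shares of 0.25 to 1, 15 analysed patients in each of 14 wards, equal ward sizes and normal ward means. If pairing explains nothing, omitting it does no harm. If the true ICC is above 0.02, the excess grows quickly. It should be corrected before outcome data are seen, but it does not threaten the validity of the trial, and better power cannot be promised as the reason for the change.

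**What to change.** - Add pair as a random intercept, with wards nested in pairs, to the mixed models for the primary and continuous secondary outcomes. Use a small-sample degrees-of-freedom method such as Kenward-Roger.
- Do not use Wald tests with the pair model. When pair variance is near zero they are anti-conservative: about 6.4% to 6.6% at ICC 0.02.
- State how pair is taken into account in the models for dichotomous outcomes.
- State that if one ward of a pair drops out, its partner stays in the analysis. A random pair term allows this.
- Report a within-pair permutation test of the primary outcome as a check. There are 2⁷ = 128 possible allocations, so the smallest two-sided p is 2/128 = 0.016.

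If the investigators prefer to ignore the matching, the protocol should say so and give the reason.

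The cost is one more model term and some effective degrees of freedom. If the matching explains little, power may be slightly lower than under the ward-only model. A random pair term is preferable to a fixed one because the fixed term always costs six degrees of freedom.
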